**Title**

Assessing the impact of using ePAQ on quality and cost of patient care in urogynaecology: an RCT

**Background to the Research**

**What is ePAQ?**

ePAQ is a web-based interactive questionnaire (electronic pelvic floor assessment questionnaire) that provides a detailed evaluation of a woman’s pelvic floor symptoms and their impact on her quality of life. Touch-screen technology has been combined with computer programming (Dot Net & SQL Server) and existing paper-based instruments to produce an interactive user-friendly system that facilitates immediate data entry, analysis and storage. The instrument has evolved during several years' collaborative work with colleagues in a range of disciplines, including Gynaecology, Medical Physics, Colorectal Surgery, Urology and General Practice, as well as involving a women’s health user-group and regular surveys of patients' views.1 Research in primary and secondary care has established the psychometric properties of the instrument.2 The system has won a National award for innovation (HITEA) and was cited in Lord Warner’s Annual Report on NHS Innovation.3 EPAQ Systems Ltd is one of the first NHS spinout technology companies to be established in the UK (created jointly with Sheffield Teaching Hospitals NHS Trust in November 2006).

More recent development work has resulted in the creation of a website, where subjects can securely and anonymously access and use the ePAQ system via the Internet. This potentially allows subjects to use system in advance of clinic appointments (as opposed to the current practice of their completing it on arrival in clinic, immediately prior to their appointment). This study aims to evaluate the impact that using ePAQ in this way may have on the efficiency and quality of patient care. Initial survey data suggest that many women attending urogynaecology clinics do have access to the Internet and would be willing to use the system on-line & in advance of clinic appointments.4 The facility is also available in the Gynaecology Unit for women without Internet access to attend specifically for supervised use of the system. The in-depth assessment provided by the ePAQ may then be used to support an initial telephone consultation with a clinician, following which patients may be directed to the most appropriate clinic, as well as being provided with information and advice and have some forms of treatment initiated (such as behavioural therapy). The proposed randomised study aims to compare outcomes in women who use the ePAQ system in this way with women who undergo standard care in the Urogynaecology Unit.

The major advantage of electronic systems, when compared with paper questionnaires, relate to the practicalities of clinical data capture. Electronic questionnaires are comparable in terms of reliability and can be superior in terms of efficiency and response rate. In addition, electronic touch-screen questionnaires have been shown to be acceptable to patients, regardless of their age or educational background. Data quality is high, even in disadvantaged and technophobic subjects and cost analysis has shown potential economic advantages.5,6,7,8,9 Pelvic floor disorders in women, such as incontinence and prolapse, share common aetiologies and commonly coexist. Estimates vary, though it is estimated that approximately 20% of adult women experience regular urinary incontinence, 5% have some incontinence of faeces and 11% suffer with prolapse.10,11,12 However, despite better understanding of these conditions, bowel, bladder, vaginal and sexual dysfunction remain understandably taboo subjects and many women still regard them as inevitable consequences of childbirth and ageing. The personal cost to individuals is high, however simple and effective treatments are increasingly available. Many disorders respond well to behavioural, physical or medical therapy and such conservative treatments are generally recommended prior to consideration of invasive investigations or surgery.13 In clinical practice, clinical assessment is central to diagnosis and management and the restoration of function, with a view to improving quality of life, is the principal aim of treatment. It is well recognised that clinical interview data may be unreliable, being based on clinicians’ rather than patients’ views of their condition. It seems appropriate therefore, to seek ways of improving clinical assessment in order to enhance the quality of care and reliably measure outcome. Many women with pelvic floor disorders are managed in the community by GPs, nurses, physiotherapists or continence nurse advisors. In secondary and tertiary care, urologists, gynaecologists, colorectal surgeons and geriatricians are likely to be involved. However, at all levels, inconsistencies in clinical assessments represent an impediment to effective communication and the multidisciplinary approach advocated by the DoH, who in 2000 recommended the following:

• Full assessment leading to first line treatment in the primary care setting, with treatment & management plans agreed with individual patients.

• The provision of an integrated continence service, bringing together agreed protocols and procedures for primary, secondary and tertiary care.

• A comprehensive continence service, at home and in homes, bringing together all relevant health disciplines.

The further development of ePAQ has the potential to substantially augment this process by using on-line assessments to support patients' initial management and triage. Using ePAQ in advance of clinic appointments may provide patients and clinicians with prompt and valuable information and assist in directing patients to the most appropriate clinics in primary and secondary care. However, such a development warrants scrutiny in terms of patient experience and cost.

**3. Specific Research Question(s) / Hypotheses**

The ePAQ is now an established part of standard care & is in routine use in the Sheffield Urogynaecology Unit; All new patients are given the opportunity to complete the questionnaire on arrival in clinic and their printed results are then used to inform the subsequent clincial consultation. The aims of this research are to measure the impact that using ePAQ *in advance* of clinic appointments in combination with a telephone consultation has on patient care. Using an RCT methodology we will specifically evaluate its impact on the following:

**i) Patients’ experience of the clinical episode**

Outcome measures: Time to first assessment, Time to initiation of treatment, Patient Experience Questionnaire

**ii) Empowerment of patients in relation to their condition and healthcare that they receive**

Outcome measure: Modified Patient Enablement Index, QQ-10

**iii) Cost & efficiency**

Outcome measures: Number & type of clinic attendances & consultations, Costs of prescriptions & investigations

**4. Proposed research method.**

**a) Study design**

Randomised controlled trial. All women who consent to participate will be randomised to one of 2 groups:

1) ePAQ + telephone consultation

or

2) Usual care

**b) Description of the methodology**

This research will follow a quantitative methodology.

**c) Time frame**

24 months

Recruitment = 12 months. Follow-up = 6 months. Data analysis & preparation of results for publication = 6 months

**d) Sample**

All women referred to STH urogynaecology services, aged > 18 and able to read and understand English will be eligible to enter the study. Potential recruits to this study will be identified by review of referral letters received, from GPs or other clinicians, by the consultant to whom the patient has been referred ([name] or [name]). It is envisaged that a minimum of 6 new patients per week will be recruited to this study.

**e) Sample size calculation**

The primary outcome for the purposes of sample size determination is the mean outcome scale score on the Patient Experience Questionnaire (PEQ) completed following the first consultation (Steine et al, 2001). 304 patients will be recruited (assuming a 20% dropout rate) to provide the 121 women needed in each group to detect significant differences between women who use ePAQ in advance of clinic appointments and women undergoing usual care (see Table 1 below).

**Table 1.**

Sample size for PEQ outcome scale at 1% and 5% significance levels and various standard deviations

|  | 1 | 2 | 3 | 4 | 5 | 6 |
| --- | --- | --- | --- | --- | --- | --- |
| *Test significance level* | 0.01 | 0.01 | 0.01 | 0.05 | 0.05 | 0.05 |
| *1 or 2 sided test?* | 2 | 2 | 2 | 2 | 2 | 2 |
| *Difference in means* | 0.5 | 0.5 | 0.5 | 0.5 | 0.5 | 0.5 |
| *Common standard deviation* | 1.2 | 1.1 | 1.0 | 1.2 | 1.1 | 1.0 |
| *Effect size* | 0.42 | 0.46 | 0.50 | 0.42 | 0.46 | 0.50 |
| *Power ( % )* | 90 | 90 | 90 | 80 | 80 | 80 |
| *n per group* | 174 | 146 | 121 | 92 | 77 | 64 |
| *Total N* | 348 | 292 | 242 | 184 | 154 | 128 |
| *Total N (with 20% dropout)* | 436 | 366 | 304 | 230 | 194 | 160 |

Steine (et al 2001) reported a mean score of 2.9 (SD 1.0) for the outcome scale of the PEQ and mean score of 5.0 (SD 1.2) for the emotion scale. If we assume an SD of 1.0 for the outcome scale and that a mean difference of 0.5 or more points between the intervention and control groups is of both clinical and practical importance, then to achieve a 90% power for demonstarting this mean difference as being statistically significant at the 1% (two sided) level will require 121 women per group (242 in total). Assumingthat 20% of patients do not return completed PEQs, then it will be necessary to recruit and randomise 304 patients (152 per group).

**Recruitment** (see flow chart: appx I)

Typically women are referred (by letter) by General Practitioners, other Hospital Specialists or Primary Care Continence Services. All referral letters will first be reviewed by the consultant (AGF or SCR) to whom the patient has been refferred. The consultant will then decide whether or not patients is suitable for study entry. Patients considered suitable by their consultant will be contacted by telephone by the Research Nurse to discuss the study (appx II). In order to prevent any significant delays in potential study patients being offered clinic appointments, patients who are not contactable by telephone within 48 hours of the reciept of the referral letter will be excluded from the study and be sent a routine outpatient clinic appointment. Patients who express no interest in participating in the study will also be sent a routine outpatient clinic appointment. Patients who express an interest in participating in the study will be sent an information leaflet about the study and a consent form (appendix III) with SAE. Women who do not respond to this within 1 week will be contacted by telephone to assess whether they wish to participate in the study. Those women who cannot be contacted at this point, or who decline study entry will be be sent a routine outpatient clinic appointment. On receipt of signed consent forms subjetcs will be entered into the study and randomised. At this point, patients randomised to standard care will be posted clinic appointments with AGF or SCR. Women randomised to ePAQ will be posted an information letter and epaq-online information leaflet inviting them to complete the questionnaire on-line and to telephone Gynae Appointments in order to arrange their telephone consultation (with AGF or SCR). Subjects in this group who are unable to complete epaq-online will use this telephone call with gynaecology appointments to arrange a separate visit to the hopsital to complete the questionnaire.

**f) Randomisation**

Randomisation will occur on receipt of signed consent forms. Allocation will be through stratified block randomisation. SW will generate a randomisation schedule, for these strata, using the STATA software. This will be held remotely by GLJ (who will not be directly involved in recruiting patients to the study). By referring to the list, she will allocate patients to either the intervention group (ePAQ + telephone consultation) or the control group (usual care). The randomised allocation will then be passed on to the research nurse who will then send the relevant information packs to each participant, relating to the arm of the study to which they have been randomised.

**Intervention Group: ePAQ clinic**

All women randomised to this arm of the study will be enetered onto the hospital PAS system under the ePAQ clinic. They will be invited by letter to complete epaq-online (and if necessary supervised ePAQ completion as a separate visit) and asked to contact Gynaecology Appointments in order to arrange their telephone consultation with AGF or SCR:

1. Letter inviting patients to complete epaq-online (including epaq-online information leaflet) & to telephone Gynaecology Appointments in order to book their telephone consultation.
2. Patient telephones Gynaecology Appointments when clerk will:
3. Ascertain whether patient has already succesfully completed epaq-online

If not: Agree & send a date, time & place to attend for supervised completion of ePAQ in hospital.

1. Agree & send (to all patients) a date, time & number for their telephone consultation
2. Scheduled telephone consultation with AGF or SCR

(supported by ePAQ report, referral letter and hospital casenotes)

1. Letter dictated to patient (including appropriate patient information leaflets & follow-up appointment)
2. Letter written to GP & referring clinician (including copy of above letter to patient)

The epaq-online information leaflet includes details of the web address for epaq-online (www.epaq-online.co.uk) with information explaining how to log-on and use the website. On completion of the questionnaire, the patient has the option of printing out a summary of her questionnaire data, which will include a summary of symptom scores in each area (urinary, bowel, vaginal and sexual). The patient is asked to forward her username and questionnaire ID to an STH email address ([contact]). Data are encrypted and anonymised (in line with good data protection practice) and can only be personalised to an individual patient by an approved clinician in receipt of the patient's username & questionnaire number, provided by the patient themselves. The clinician will use these results along with the patient's own casenotes and original referral letter to support the subsequent telephone consultation.

**Non-intervention (control) group: Usual care**

All women randomised to this arm of the study will be given an appointment to attend the urogynaecology clinic. 'Usual care' currently includes the option of completing the ePAQ on arrival in clinic, immediately prior to the clinical consultation. As is currently standard practice, the results of the ePAQ will be used to inform & support clinical assessment, however, as the ePAQ is used *immediately* prior to the clinical consultation, patients cannot be triaged or receive any additional information on the basis of their questionnaire results.

**Outcome Measures**

In order to achieve uniformity of approach (between ePAQ and control groups) outcome questionnaires (PEQ, PEI & QQ-10) will be posted to patients *immediately* after their first consultation. Patients will be asked to complete and return these by post.

**Primary Outcome Measure**

**Patient Experience Questionnaire**

The primary outcome for the purposes of sample size determination is the mean outcome scale score on the Patient Experience Questionnaire (PEQ) (Steine et al, 2001) (Appendix 6). The PEQ will be used to evaluate whether using ePAQ in combination with a telephone consultation results in any difference in the patient experience when compared with standard care. In order to evaluate the impact of using ePAQ in this way, we ask all patients (in both arms of the study) to complete the PEQ after their first clinical consultation.. The PEQ was developed and validated specifically to measure patients’ experience of interaction, emotion and consultation outcome. It contains 16 items in four dimensions, including 1) communication, 2) emotions 3) short-term outcome and 4) barriers. Three scales are scored from 1 to 5, and the emotion scale runs from 1 to 7. A high score represents a good communication experience, positive emotions, positive consultation outcome and a lack of communication barriers.

**Secondary Outcome Measures**

**1. Number and type of referrals**

The total number and individual type of referrals made will be used to evaluate the impact of ePAQ on the referral patterns and clinical visits made within the continence care pathway. At 6-month follow-up we will measure the number and type of referrals made on behalf of that patient; i.e. primary care (community nursing, community physiotherapy, GP, district nurse, practice nurse) and secondary care (gynaecology, urology, colorectal surgery, physiotherapy). These data will be collected in both groups using a standard proforma (appx VII).

**2. Number and type of prescriptions**

The number and type of prescriptions made will be collected to evaluate whether the use of ePAQ in advance of clinic appointments has any influence on the number of prescriptions made within the continence care pathway. These data will be collected at the 6-month follow-up on a proforma (appx VII) and supported by looking through the appropriate medical records. The prescribing of first line treatment will be categorised as (a) drug treatment (b) physiotherapy (c) behavioural therapy and (d) surgery.

**4. Modified Patient Enablement Index**

A modified version of the PEI will be administered (Howie et al, 1997; 1998) (Appendix 7). This validated instrument contains 6 items asking about the patient’s ability following a consultation to 1) cope with life 2) understand their illness, 3) cope with their illness, 4) keep themselves healthy, 5) feel confident about their health and 6) help themselves.

**5. Cost effectiveness**

The economic analysis will estimate the NHS costs of providing assessment and care up to six months in both arms of the study, and cost effectiveness by an incremental cost per quality-adjusted life year (QALY). These costs will include the costs of using ePAQ + telephone consultations, referrals, prescriptions (drugs / appliances / pads) and treatments. A broader societal costing will also be undertaken to consider costs to the patients and the economy in terms of private expenditure and time taken off work, respectively. These additional data will be in the standard proforma posted to both groups of patients at 6 months (appx VII).

Data on the use of the health services will be collected for each patient from records accessed from Trust and Primary Care practices. Data on private and societal costs will be gathered using patient-completed questionnaires at 6 months (appendix VII). Such patient-completed questionnaires are used in nearly all economic evaluations. Examples of questions include; "In the last 6 months, have you spent any money on anything because of bladder, bowel or vaginal problems?", "If yes, what did you spend it on?" "How much have you spent on each?", and "In the last 6 months, how many days have you needed to take off work because of bladder, bowel or vaginal problems and their treatment / care?" Costs will then be calculated using unit costs from routine sources (Curtis & Netten 2004, NHS Reference Costs and the British National Formulary). The costs associated with using ePAQ + telephone consulations compared with usual care will be estimated through a micro-costing study conducted during the first full 2-week period following recruitment of the 200th patient to the study.

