**5. Analysis of cost-effectiveness**

The incremental cost-effectiveness ratio constructed from the cost and QALY data will be presented along with its associated cost-effectiveness acceptability curve. Separate analyses will be undertaken for NHS costs and the broader societal costs. One-way sensitivity analysis will be undertaken to assess the robustness of the results to changes in those variables where significant uncertainty remains, e.g. price of using ePAQ. Threshold analysis will also be undertaken to assess whether variation in any service characteristics exert significant influence on cost-effectiveness. These results can then be reformulated in a way that is clear to all service providers (Goodacre & Dixon 2005). Sub-group analysis will also be undertaken to assess the cost-effectiveness of using ePAQ in women of different age groups (e.g. under and over 50s) and with clinical conditions (e.g. incontinence and prolapse).

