**6. Analysis of patient enablement**

The PEI is a six-item self-complete questionnaire, which generates a score with a 0 to 12 range, with a higher score indicating more patient satisfaction / enablement. The PEI is to be posted to patients in both arms of the study, immediately after their fist consultation. A 2 independent samples t-test will be used to compare mean PEI scores between the groups (ePAQ group vs and usual care) in this parameter. A 95% confidence interval (CI) for the mean difference in this parameter between the ePAQ and usual care groups will also be calculated.

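### The protocol plans a cost per QALY but names and schedules no utility measure, so QALYs cannot be computed from the data collection it describes

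*Protocol*

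**What the plan says.** Under Secondary Outcome Measures, item 5 (Cost effectiveness), the protocol sets out to estimate NHS costs up to six months in both arms and "cost effectiveness by an incremental cost per quality-adjusted life year (QALY"). Under Planned Analysis, item 5, it states: "The incremental cost-effectiveness ratio constructed from the cost and QALY data will be presented along with its associated cost-effectiveness acceptability curve". Separate NHS and societal analyses, one-way sensitivity and threshold analyses, and subgroups by age and clinical condition follow from that.

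On data collection:

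- The Outcome Measures section says that "outcome questionnaires (PEQ, PEI & QQ-10) will be posted to patients" straight after the first consultation. The Reducing bias section repeats this.
- For the 6-month contact, the Cost effectiveness section says: "Data on private and societal costs will be gathered using patient-completed questionnaires at 6 months". The referral and prescription sections use the same proforma (appendix VII) for those counts.
- Before randomisation, the Recruitment section describes posting an information leaflet and a consent form with a return envelope.
- The opening paragraph of Planned Analysis says that other secondary outcomes are assessed at randomisation and at 6 months. It allows adjustment for baseline differences, including differences in health-related quality of life. It names no instrument.

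**The concern.** A QALY is time weighted by a preference-based utility. To estimate it over six months, each woman needs a utility at the start and at the end, or a validated way of deriving one from something else she completes. The protocol sets out the cost side with care: records, a patient questionnaire, unit-cost sources and a micro-costing exercise. It gives no source for the utility side.

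This goes beyond detail that a statistical analysis plan can supply. Such a plan can define how QALYs are calculated from responses, but it cannot create responses that were never requested. Once a woman has been randomised and has had her consultation, her baseline utility cannot be recovered.

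**Working it through.** The protocol gives no figure for the QALY analysis, so there is nothing numerical to reproduce. The check is whether each quantity in the planned ratio has a data source.

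**What the ratio needs**

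- ICER = (mean cost, ePAQ arm − mean cost, usual care) ÷ (mean QALY, ePAQ arm − mean QALY, usual care).
- With utilities u0 at baseline and u6 at six months, the usual area-under-the-curve QALY is 0.5 year × (u0 + u6) ÷ 2 = 0.25 × (u0 + u6).

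The inputs are therefore cost, u0 and u6 for each woman.

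**Where each input could come from**

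1. *Cost.* The Cost effectiveness section supplies it from Trust and primary care records, the 6-month patient questionnaire, unit costs and micro-costing. The source is adequate.
2. *PEQ.* This measures consultation experience: "It contains 16 items in four dimensions, including 1) communication, 2) emotions 3) short-term outcome and 4) barriers". It is sent once, after the first consultation. It is not described as preference-based and gives neither u0 nor u6.
3. *PEI.* It "generates a score with a 0 to 12 range, with a higher score indicating more patient satisfaction / enablement". It is sent once, after the first consultation, and asks about ability following that consultation. It gives neither u0 nor u6.
4. *QQ-10.* The aims list it under patient empowerment. It is sent at the same single time, and no utility scoring is described.
5. *Six-month proforma.* As described, it covers referrals, prescriptions, private spending and days off work. The example questions concern money and work days. No source of u6 is described.
6. *Consent pack.* Only a leaflet and a consent form are described. No source of u0 is described.
7. *ePAQ.* It covers pelvic floor symptoms and their effect on quality of life, but no mapping to utility is mentioned. Women complete it after randomisation. The intervention arm does so before the telephone consultation. For usual care it is an option on arrival in clinic. No 6-month completion is scheduled. It cannot stand in for u0 and u6 as the procedures are written.
8. *Baseline quality of life in Planned Analysis.* The text assumes that such measurements exist. Neither Recruitment, Randomisation nor Outcome Measures says what they are or when they are taken.

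The numbering of the secondary outcomes runs from 2 to 4. The gap does not supply the missing measure, because none of the six numbered analysis subsections deals with a health-related quality of life instrument.

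**Result.** Cost has a source; u0 and u6 have none. The numerator of the ICER can be calculated from what is described, and the denominator cannot.

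**What is and is not touched.** The aims define cost and efficiency by attendances, consultations, and costs of prescriptions and investigations, and none of these needs a utility. The same holds for the planned comparisons of referrals, consultations and prescriptions and for the NHS and societal cost estimates. The PEQ primary outcome and the sample size of 121 per group (304 randomised) do not depend on QALYs.

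**The case against.** The strongest reply is that silence in the visible text does not prove absence. Appendix VII is not shown, and the protocol introduces its questions as examples, so a utility instrument could sit in that booklet. The Planned Analysis section states that other secondary outcomes are assessed at baseline and 6 months and speaks of baseline quality of life. Cost effectiveness is a secondary outcome, so a utility measure may have been intended at both times.

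Much of this stands. A reader might infer that no woman will provide QALY data and that the economic analysis is impossible. The documents do not support that. They show only that no instrument is named or scheduled in the text, and an unseen appendix cannot be used as evidence of a gap. Nor can it be said that women receive nothing before randomisation, since a consent pack is posted. The supportable statement is that no utility questionnaire is described as part of it.

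The reply does not remove the problem. A utility item in appendix VII would supply six months only. The sentence in Planned Analysis is not a workable schedule: it names no instrument and matches no step in recruitment or follow-up. It also cannot apply to every secondary outcome, because the PEI asks about ability after a consultation and so cannot be taken at randomisation.

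It is also fair to say that the choice of instrument and the form of baseline adjustment can be settled in the analysis plan. That some instrument will be used, and when, cannot wait for it.

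**Conclusion.** The point holds in this form: the protocol commits to a cost per QALY, an ICER and an acceptability curve, and the data collection it describes yields no QALYs. The analysis section presupposes baseline quality of life measurements that no procedure collects.

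The size is structural rather than numerical. One planned secondary analysis, in its NHS and societal versions, lacks its denominator, and so do the acceptability curve, the sensitivity and threshold analyses and the subgroups that depend on it. A reader might infer that the whole cost and efficiency question is lost. It is not, because its listed outcome measures are resource use and costs, which are collected.

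Confidence is high that no utility measure is named or scheduled in the text. Whether appendix VII contains one is unknown, and the conclusion is conditional on that. The matter has to be settled before the first woman is randomised, because a missed baseline cannot be made good.

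**What to change.** 1. Name a short preference-based utility questionnaire, for example EQ-5D or SF-6D, as the source of the QALYs.
2. Put it in the consent pack so that it comes back with the signed consent form. Randomisation occurs on receipt of that form, so the answers are given before allocation is known.
3. Repeat it with the 6-month proforma already posted to both arms.
4. State that the QALY comparison will be adjusted for baseline utility.
5. Reconcile the baseline and 6-month statements in Planned Analysis with the Recruitment, Outcome Measures and Cost effectiveness sections, so that each measure has one stated time and route.

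If appendix VII already holds such a measure, name it in the protocol text and add the baseline administration.

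If the sponsor does not want to add a questionnaire, replace the cost-per-QALY text in both cost-effectiveness sections with a cost-consequence analysis that sets the NHS and societal cost differences beside the PEQ difference.

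The cost is one extra short questionnaire in two mailings already planned, possible licence registration and a protocol amendment. No extra patients or visits are needed. The cost-consequence route needs only the amendment, but gives up the ICER and the acceptability curve.
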